
### Statistical analysis and sample size

We anticipate 150 participants will need to be randomised to achieve a sample size of 60 participants per arm to complete day 14. This allows for 20% attrition, consonant with the palliative care literature and previous RCTs. The sample size calculations are based on an effect size of ≥ 6 improvement in TSDS for the active arm compared to placebo, 80% power, 1:1 randomisation scheme, a type 1 error of 5% (two-tailed) and a standard deviation of 11.6. These numbers are based on the existing literature which suggests the minimum clinically important difference in the TSDS for a similar patient population to be 5.7 [6]. As such, we have elected to use an improvement of the TSDS of ≥ 6 as a clinically significant change. The Stata software (StataCorp. 2013. Stata Statistical Software: Release 13. College Station, TX: StataCorp) was used to estimate the sample size.

The study is powered to detect the superiority of arm 1 over arm 2 (placebo). Superiority will be determined by comparison at day 14 with appropriate baseline adjustment.

Participant demographic and clinical characteristics will be used to generate descriptive data and frequency distributions. For the primary outcome, the difference in change in TSDS between the treatment groups will be assessed using *t*-tests for unadjusted differences and ordinary least squares regression to adjust for baseline values [17]. Generalised estimating equations or mixed models will be used for secondary outcomes with multiple measurements per participant, accounting for within-subject correlation and effects due to the centre. Covariate influence will be explored.

An interim analysis will be completed following 50% completion of day 14. This analysis will be by an independent biostatistician. They will be blinded to treatment allocation. A report will be provided to the investigators and the Data Safety Monitoring Board (DSMB). This is to monitor participant safety. AEs and SAEs will be categorised by type and severity. The frequency of such adverse effects will be compared between the groups using the chi-squared tests and logistic regression to adjust for any relevant group differences.

If the interim analysis shows a significant difference, the investigators and the DSMB will be unblinded to the study groups and make any stopping decision on the basis of the nature of any AEs and/or SAEs and ethical grounds, as well as consideration of any statistical differences between the groups. Grounds for stopping on evidence of clear benefit will be considered. The Peto approach will be taken with symmetric stopping boundaries at *p* = 0.001.

A detailed statistical analysis plan will be prepared and ratified by the DSMB.

The sleep part of the study will be powered to detect a mean difference of ≥ 6 on the ISI between the intervention arm and the placebo group. Assuming a 1:1 ratio of active and placebo treatment, a mean difference between the groups (reduction in ISI score) of ≥ 6, a standard deviation of the difference of 8, alpha of 0.05 and power of 80%, 58 participants, 29 in each group, would be needed. To allow for 20% attrition, 74 subjects (37 in each group) will be recruited.

All protocol modifications will be approved by the relevant Human Research Ethics Committee and communicated to all investigators, and trial registration information updated. All investigators will have access to the final dataset. The datasets used and/or analysed during the study will be available from the corresponding author upon reasonable request.

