### Randomisation

Eligible patients will be assigned in equal numbers to one of the two arms at random. Random number tables will be used for computer-generated randomisation schedules at an independent location by the staff not otherwise involved in the trial. A central registry will hold treatment allocations as determined by a permuted block randomisation schedule. Each site will have its own block randomisation schedule leading to even allocation to each treatment arm within each site. Actions to minimise the risk of bias are detailed in Additional file 1: Table S1.

Following fully informed written consent, the procedure will be as follows:The research pharmacy will be notified of a new participant.The investigator will complete a trial prescription with the participant’s study ID number and provide this to the trial pharmacy.Based on the randomisation schedule, the pharmacist will dispense the appropriate medication in a bottle labelled ‘THC:CBD 10 mg:200 mg/mL or placebo’.Participant ID, allocation number, date of request, preparation and dispensing will be recorded by the site pharmacist for each instance.

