### Outcomes and assessment tools

The primary outcome is the change from the baseline of total ESAS TSDS at day 14. The ESAS is a nine-item inventory rated on an 11-point scale anchored at 0 (no problem) to 10 (worst imaginable of this problem). It assesses both physical and psychological symptoms, plus general well-being [6]. It has been validated in the assessment of symptoms in cancer patients [10].

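### Randomisation is blocked within site but the stated primary model omits site, so if sites differ the day-14 test is conservative and a little precision is given up

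*Protocol article*

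**What the plan says.** **Design.** Protocol article, Randomisation: "Each site will have its own block randomisation schedule leading to even allocation to each treatment arm within each site". Site is therefore a stratification factor.

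**Primary outcome.** Outcomes and assessment tools: "The primary outcome is the change from the baseline of total ESAS TSDS at day 14".

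**Primary analysis.** Statistical analysis and sample size names t-tests for the unadjusted difference and "ordinary least squares regression to adjust for baseline values". The superiority criterion is in the same section: "Superiority will be determined by comparison at day 14 with appropriate baseline adjustment". Neither statement mentions site.

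**Secondary analysis.** The next step in that section uses generalised estimating equations or mixed models for secondary outcomes measured repeatedly, "accounting for within-subject correlation and effects due to the centre". The paragraph on modelling closes with "Covariate influence will be explored", which does not commit to a site term.

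**The concern.** An analysis should normally reflect the restrictions placed on the randomisation. Balancing the arms within each site stops differences between sites from contributing to the chance error of the treatment comparison. A model without site does not know this. It counts between-site variation as residual noise and reports a standard error larger than the real one.

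The article is also uneven with itself. TSDS at days 7, 21 and 28 is a secondary outcome with repeated measurements, so its model accounts for centre. TSDS at day 14 is the same scale in the same participants and is the one confirmatory comparison, yet its stated model does not.

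Site differences are plausible on the article's own description. Under Study setting, usual care follows local practice, rural and remote participants join through the teletrial model, and both inpatients and outpatients are eligible. At stake is some precision in the confirmatory result, and a test that is stricter than the stated 5%.

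**Working it through.** **Inputs from the article** (Statistical analysis and sample size): a 6-point "improvement in TSDS for the active arm compared to placebo, 80% power, 1:1 randomisation scheme", two-sided alpha 0.05, SD 11.6, 60 completers per arm, 150 randomised, 20% attrition.

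**Inputs not in the article, therefore assumed:** the residual ICC (the share of outcome variance lying between sites after baseline adjustment), and the number and size of sites.

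**Step 1. Reproduce the planned size.** The normal approximation gives 59 per arm. The t-test gives 79.6% power at 59 and 80.2% at 60, so 60 per arm is right. Then 120 / 0.8 = 150. The calculation is a plain two-sample one with no site term.

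**Step 2. Effect of omitting site, with exact balance within site.**

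- Standard error reported without site: SE = 11.6 × √(2/60) = 2.118.
- True standard error: SE × √(1 − ICC). The reported value is too large by the factor 1/√(1 − ICC).
- Type I error without site: 2Φ(−1.96/√(1 − ICC)).
- Power without site: Φ((6/SE − 1.96)/√(1 − ICC)), where 6/2.118 = 2.833.
- Power with site: Φ(2.833/√(1 − ICC) − 1.96).

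| Residual ICC (assumed) | SE too large by | Type I error without site | Power without site | Power with site | Difference (points) |
|---|---|---|---|---|---|
| 0 | 0% | 5.0% | 80.9% | 80.9% | 0 |
| 0.02 | 1.0% | 4.8% | 81.1% | 81.6% | 0.5 |
| 0.05 | 2.6% | 4.4% | 81.5% | 82.8% | 1.3 |
| 0.10 | 5.4% | 3.9% | 82.1% | 84.8% | 2.6 |
| 0.20 | 11.8% | 2.8% | 83.6% | 88.6% | 5.1 |

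In TSDS points at ICC 0.10, the 95% CI half-width is 1.96 × 2.118 = 4.15 without site and 4.15 × √0.90 = 3.94 with it, a difference of about 0.2 on a 0 to 90 scale.

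**Step 3. Simulation with baseline in both models and with attrition.** 150 randomised in blocks of 4, 20% random dropout, 4,000 replicates per setting. The Monte Carlo standard error is about √(0.05 × 0.95/4000) = 0.3 points for type I error and √(0.8 × 0.2/4000) = 0.6 points for power.

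| Sites | ICC | Type I: without / with site | Power: without / with site |
|---|---|---|---|
| 4 | 0 | 4.6% / 4.6% | 79.2% / 79.1% |
| 4 | 0.05 | 4.0% / 4.4% | 81.0% / 82.2% |
| 4 | 0.10 | 4.0% / 4.7% | 80.1% / 82.6% |
| 4 | 0.20 | 3.6% / 4.8% | 83.8% / 88.2% |
| 8 | 0 | 5.3% / 5.2% | 80.3% / 79.5% |
| 8 | 0.05 | 4.7% / 4.8% | 80.1% / 80.7% |
| 8 | 0.10 | 4.2% / 4.9% | 80.6% / 82.1% |
| 8 | 0.20 | 3.7% / 4.9% | 82.6% / 87.0% |

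Dropout disturbs the balance within sites, so the test is less conservative than Step 2 implies. This is clear at ICC 0.20 (3.6% to 3.7% against 2.8%) and within simulation error at lower values.

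With only two sites, of 100 and 50 (assumed), power is equal at ICC 0.02, differs by less than 1 point at 0.05 and by about 1.2 to 1.4 points at 0.10.

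**The case against.** The strongest reply is that covariate choice belongs in the statistical analysis plan, which the article says will be prepared and ratified by the DSMB, and that a condensed article silent on site has not excluded it. This stands in part: the unseen plan may already include site. But the article is not simply silent. It names the primary model and its adjustment, and then attaches centre effects to the secondary models only. Read as written, the primary model has no site term.

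The second reply is that the effect is conditional, small and conservative. That stands in full and sets the limits of this point. A reader might infer more, in three ways:

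- **That the primary standard error is certainly too large.** The article gives no ICC, no number of sites and no site sizes. If sites do not differ after baseline adjustment, the overstatement is zero.
- **That the trial is underpowered.** The planned 80% comes from an unadjusted two-sample calculation with SD 11.6, and it reproduces. Without site, power in Step 2 is 80.9% or higher throughout. The simulated values slightly under 80% occur only at ICC 0, where omitting site costs nothing, and are within about 1.3 Monte Carlo standard errors of 80%. The loss is only relative to a better model.
- **That the result would be biased or falsely positive too often.** Omitting site after balanced allocation within site does neither. A significant result from the stated model would remain valid.

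**Conclusion.** The point holds in conditional form. The stated primary analysis leaves out the factor by which the trial stratifies its randomisation, while the secondary models include it. For an assumed residual ICC of 0.02 to 0.10, the standard error is about 1% to 5% too large. Type I error is about 4.8% to 3.9% under exact balance, and nearer 5% once attrition disturbs that balance. Between 0 and 3 points of power are forgone, depending also on the number of sites. An ICC of 0.20 would raise the loss to about 4 to 5 points, but nothing in the article points to a value that high.

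This is a modest inefficiency in the one confirmatory comparison. It is worth correcting because the correction is nearly free and the plan has little slack: 80.2% power at 60 per arm by t-test.

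**What to change.** Make the confirmatory day-14 analysis an ordinary least squares model with treatment, baseline TSDS and randomising site. Define site as the unit that holds its own block schedule, so that every teletrial participant belongs to the schedule from which they were allocated. Use either fixed site effects, with very small sites pooled by a stated rule, or a random site effect. Fix the choice and the pooling rule before unblinding, so that the choice between models cannot depend on the results. Keep the t-test as a supportive, unadjusted summary.

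Use the same model for any interim efficacy test against the p = 0.001 boundary. With site omitted and a residual ICC of 0.10, that boundary would act at about 2Φ(−3.29 × 1.054) ≈ 0.0005.

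The cost is one line of analysis-plan wording and one degree of freedom per additional site. If sites turn out not to differ, the simulation puts the price at 0.1 points of power with 4 sites and 0.8 points with 8, about the size of the simulation error. The sample size need not change.

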Secondary outcomes include the following:Patient-determined effective dose of THC/CBD 1:20 formulation, defined as the dose that achieves symptom relief with acceptable side effects.ESAS TSDS at days 7, 21 and 28.Physical and emotional ESAS scores at each time point.Physical scores will be measured by the AKPS and Resource Utilisation Groups-Activities of Daily Living Scale (RUG-ADL). The AKPS is a validated variant of the Karnofsky Performance Status [11]. The Australian version can be applied to both inpatients and outpatients and is sensitive to changes in function over time. The RUG-ADL is an instrument developed for the measurement of nursing dependency [12]. The ADL scale measures patients’ needs for assistance in activities of daily living (eating, bed mobility, transferring and toileting).Individual symptom scores (descriptive analysis only).Oral morphine equivalent (OME), average use at baseline and weekly.Patient Global Impression of Change (PGIC), days 7, 14, 21 and 28.This is a subjective measure of symptom change completed by the participants themselves [13].Clinical Global Impressions (CGI) scale, days 7, 14, 21 and 28.This is a subjective measure of symptom change completed by the investigating clinician [13].The Depression, Anxiety and Stress Scale (DASS-21).DASS-21 is a self-reported 21-item scale, 7 questions per sub-item questionnaire measuring depression, anxiety and stress [14]. The DASS-21 will be used for assessment at baseline (day 0) and at days 14 and 28.EORTC score QoL baseline and days 14 and 28.This is a QoL measure found valid for use in a wide variety of cancer populations. To reduce patient burden, we will use the 15-question subset commonly used for the palliative care population [13].NCI common terminology for adverse events V4.03, days 2, 4, 7, 9, 11, 14, 16, 18, 21, 23, 25 and 28.The NCI CTCAE is a severity grading system for adverse events [15]. Adverse events relate to an unfavourable or unintended sign, symptom or disease temporarily associated with a medical treatment or a procedure which may not be related to the medical treatment or procedure. The CTCAE has a grading of 1 (mild) to 5 (death). The known common adverse events associated with cannabinoids are confusion, somnolence, paranoia, anxiety, mood changes, psychosis, hypertension, tachycardia, hyperhidrosis, nausea, vomiting and abdominal pain.The study will assess adverse events (AE) and serious adverse events (SAE) using the criteria of the NCI CTCAE V4.0. The known common AEs associated with THC/CBD will be sought at each time point. A comprehensive clinical review which includes the compilation of a concurrent medication list will occur at days 0, 7, 14, 21 and 28. This will include over-the-counter and complementary medications in addition to prescribed medications.SleepESAS (with additional sleep score item) at days 0, 7 and 14.Objective measure of sleep via actigraphy. These measures will include total sleep time, sleep efficiency, wake after sleep onset and sleep onset latency (min). Participants will wear an accelerometer on their wrists for 14 days to measure circadian activity, sleep quality and quantity. Actigraphy has been found to be a validated, objective way to measure sleep outcomes [8].The ISI is a measurement tool that assesses sleep quality. It consists of 7 questions each of which are scored 0 (best) to 4 (worst) with respect to sleep quality [16]. Interpretation is by the total score which classifies 0–7 as no clinically significant insomnia, 8–14 as subthreshold insomnia, 15–21 as clinical insomnia of moderate severity and 22–28 as severe clinical insomnia. The Sleep Numerical Score is an 11-point numerical rating scale where 0 is the best possible sleep, and 10 is the worst possible sleep.

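### The interim rule sends between-group results to the investigators and unblinds them on an undefined significant difference, while the double-blind trial may continue

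*Protocol article*

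**What the plan says.** All of the interim rules stand in the protocol article under Statistical analysis and sample size.

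- Timing: "An interim analysis will be completed following 50% completion of day 14".
- Analyst: an independent biostatistician who does not know the treatment allocation.
- Recipients: "A report will be provided to the investigators and the Data Safety Monitoring Board (DSMB"; the stated purpose is participant safety.
- Safety comparison: "The frequency of such adverse effects will be compared between the groups using the chi-squared tests and logistic regression", with no significance level.
- Unblinding: "If the interim analysis shows a significant difference, the investigators and the DSMB will be unblinded to the study groups".
- Decision: these same parties then "make any stopping decision on the basis of the nature of any AEs and/or SAEs and ethical grounds", and also weigh statistical differences between the groups. Stopping for clear benefit may be considered.
- Boundary: "The Peto approach will be taken with symmetric stopping boundaries at" *p* = 0.001.

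Elsewhere, the title calls the trial double-blind. The Discussion points to the measures taken to keep the blind and says they protect the treatment effect estimate from bias. Under Outcomes and assessment tools, the CGI is scored at days 7, 14, 21 and 28: "This is a subjective measure of symptom change completed by the investigating clinician".

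**The concern.** Interim comparisons are normally kept from those who treat and assess participants, so that later assessments are not coloured by earlier results. Here the rule does the opposite in two steps. The between-group report reaches the investigators whatever it shows. If it shows something significant, they are also told which group is which, and they share the stopping decision with the DSMB.

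Stopping is only one possible outcome of that decision. If the trial goes on, investigators may know how the active arm is doing while about half of the day-14 data are still to be collected. Nothing in the article restores or protects their blind after that.

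The exposed data are the CGI, which the investigating clinician completes, and adverse events, which the data collection table assigns to the study nurse and medical officer. The primary outcome is reported by the patient, but during a titration in which patients may consult research staff about their dose. If unblinded staff take part in this, the route to the primary outcome is indirect but open.

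**Working it through.** **1. The plan's own figure.** Inputs from Statistical analysis and sample size: difference 6, SD 11.6, two-sided alpha 0.05, power 80%, attrition 20%.

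n per arm = 2 × (1.960 + 0.842)² × 11.6² / 6² = 58.7, so 59. The t-test version gives 59.65, so 60. Then 2 × 60 / 0.80 = 150. The stated sample size reproduces.

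**2. Size of the interim.** Half of 120 day-14 completers is 60, or 30 per arm.

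**3. What the text ties to what.**

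| Element | Endpoint given | Level given | Who acts |
|---|---|---|---|
| Unblinding | none | none | investigators and DSMB |
| Stopping boundary | none | p = 0.001 | investigators and DSMB |
| Adverse event comparison | adverse events | none | reported to investigators and DSMB |

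The 0.001 level is written for stopping. No sentence applies it to unblinding.

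**4. How often the two could diverge.** Assumption: significant means two-sided p < 0.05 on day-14 TSDS. The article states neither the level nor the endpoint for this trigger.

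Standard error = 11.6 × √(2/30) = 2.995. The noncentrality is 6 / 2.995 = 2.003 for 6 points and 3 / 2.995 = 1.002 for 3 points. With T a noncentral t on 58 degrees of freedom and c the two-sided critical value at level a, P(p < a) = P(T > c) + P(T < −c).

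| True difference | P(p < 0.05) | P(p < 0.001) | Unblinded, boundary not crossed |
|---|---|---|---|
| 6 points (planned) | 0.504 | 0.084 | 0.504 − 0.084 = 0.420 |
| 3 points | 0.166 | 0.010 | 0.166 − 0.010 = 0.157 (before rounding) |
| 0 | 0.050 | 0.001 | 0.050 − 0.001 = 0.049 |

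If 50% were instead taken of the 150 randomised (75, or 37.5 per arm), the last column becomes 0.470, 0.184 and 0.049.

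**5. The other reading of the trigger.** If significant means p < 0.001 on TSDS, the last column is zero by definition. The chance of triggering on TSDS falls to 0.084, 0.010 and 0.001 at 30 per arm. When it does trigger, the investigators are still unblinded before a decision that may be to continue.

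**The case against.** The strongest reply is that the rule is milder than it looks. The analyst is blinded, so the report most naturally compares coded groups, and being unblinded to the study groups may mean only that the codes are opened. The Randomisation section keeps allocations in a central registry, and bottles carry a label that does not reveal the arm. A reader might infer that investigators learn each patient's allocation; the article does not say this. The reply therefore lowers the likely harm but does not remove it. Knowing mid-trial which arm is ahead, or which has more adverse events, is still knowledge that those rating later participants should not have.

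Second, p = 0.001 is the only level given specifically for the interim and stands in the same short paragraph, so it may be what significant means. That is a fair reading, and on it the efficacy gap vanishes. It changes how often the rule fires, not who is unblinded.

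Third, roles are not fully spelled out. Only the CGI is assigned to the investigating clinician. That the same people also advise on titration and grade adverse events is an inference.

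Three stronger inferences are tempting and should not be drawn:

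- *The type I error is inflated.* The article sets stopping at 0.001. One look at 0.001 and a final test at 0.05 give an overall alpha of 5.02%, which is negligible inflation.
- *Adverse event tests will often break the blind by chance.* Twelve common events are listed, and 1 − 0.95¹² = 46%, but the article does not say that each is tested separately at 5%, and independence would also have to be assumed.
- *The analysis plan may be ratified after the DSMB has seen unblinded data.* The article says "A detailed statistical analysis plan will be prepared and ratified by the DSMB" without a date. A condensed article may leave that to the full documents.

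The analysis plan and the supplementary table on bias are not shown. They may add safeguards, but they would then have to override a rule that the article states outright.

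**Conclusion.** The point stands in a limited form. The article states, as a rule, that investigators receive between-group interim results and are unblinded to the groups on a significant difference whose endpoint and level are undefined. They then share a discretionary decision that may be to continue. This conflicts with the double-blind title and with the Discussion's reliance on blinding.

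The frequency depends on how the trigger is read. At p < 0.05 on day-14 TSDS with 30 per arm and SD 11.6, the chance of unblinding without crossing 0.001 runs from 5% (no effect) through 16% (3 points) to 42% (the planned effect). At p < 0.001 on TSDS it is zero. Adverse event triggers would add to either figure by an amount the article does not allow one to calculate.

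The problem is operational bias, chiefly in the CGI and the adverse event data, and not error-rate control. The article supports disclosure at group level; disclosure of individual allocations is not established.

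**What to change.** Amend the protocol and the DSMB's terms as follows:

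- Send between-group interim output to the DSMB only.
- Let the DSMB obtain arm identity whenever it asks, without waiting for a significant test.
- Give investigators only the recommendation: continue, modify or stop.
- Define the efficacy trigger as p < 0.001 on day-14 TSDS, so that it coincides with the stated boundary.
- Leave safety to DSMB judgement.

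If the interim has already been run, report who was unblinded, to what level (group or individual) and when.

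The cost is a wording amendment, with no added patients, visits or analyses. The downside is that investigators lose sight of interim comparisons. The change must precede the interim to be of full use, because unblinding cannot be undone.

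### The interim look is meant to monitor safety, yet the DSMB's unblinding and stopping decision wait on an undefined significant difference, and the investigators are unblinded with it

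*Protocol article*

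**What the plan says.** All of this is in the Protocol article, under Statistical analysis and sample size, unless noted.

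- Timing: "An interim analysis will be completed following 50% completion of day 14".
- Purpose: "This is to monitor participant safety". Adverse and serious adverse events are compared between groups by chi-squared tests and logistic regression.
- Who sees what: a biostatistician who does not know the allocation does the analysis and reports to the investigators and the DSMB.
- Trigger: "If the interim analysis shows a significant difference, the investigators and the DSMB will be unblinded to the study groups". The stopping decision follows in the same sentence. It rests on the character of the adverse events and on ethics, with statistical differences also considered. No level or endpoint is attached to the word significant.
- Boundary: after a sentence allowing a stop for clear benefit, "The Peto approach will be taken with symmetric stopping boundaries", set at p = 0.001. The endpoint is not named, and no separate boundary for harm is given.
- Elsewhere (Data collection and management): the DSMB has primary responsibility for monitoring adverse events and reviews them at least every six months. The text does not say whether it sees them by arm.

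**The concern.** A very strict interim boundary protects the type I error of an early claim of benefit. It has no such role for harm, where strictness only delays recognition. Here the safety judgement is also placed behind a test. As written, the DSMB weighs the nature of the events with knowledge of the arms only once a difference is significant. Until then it holds a report from someone who does not know which arm is which. With about half the completers, a significance test has little power for moderate harm, so a non-significant result is weak reassurance in a frail population.

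The same sentence unblinds the investigators. If the DSMB then lets the trial continue, the people recruiting, supporting titration and rating the Clinical Global Impressions scale would know the allocation.

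**Working it through.** **Inputs from the protocol.** SD 11.6, difference 6 TSDS points, 80% power, two-sided 5%, 60 completers per arm, 150 randomised, boundary p = 0.001, minimum clinically important difference (MCID) 5.7.

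**Assumptions.**
- The 0.001 is two-sided.
- The interim has 30 per arm (half of 60). As a sensitivity case it has 37 per arm (half of 150 is 75; equally, 60 completers at 20% attrition come from 60/0.8 = 75 randomised).
- The protocol gives no adverse-event risks by arm, so those below are illustrative.

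**Step 1: reproduce the plan's sample size.** n per arm = 2 × (1.960 + 0.842)² × 11.6² / 6² = 58.7, so 59 by the normal formula. The t-based value is 59.65, so 60. Then 120/0.8 = 150. The stated figures reproduce.

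**Step 2: what p ≤ 0.001 requires at 30 per arm.**
- TSDS: SE = 11.6 × √(2/30) = 2.995. The critical t on 58 df at 0.0005 is 3.466. The critical difference is 3.466 × 2.995 = 10.4 points, against the MCID of 5.7.
- Events: by Pearson chi-squared, the smallest imbalances are 10/30 vs 0/30, 12/30 vs 1/30 or 14/30 vs 2/30. For example, with 14 vs 2 the pooled risk is 16/60 = 0.267, and z = 0.400 / √(0.267 × 0.733 × 2/30) = 3.50, above 3.29. With 13 vs 2, z = 3.28, which falls just short.

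**Step 3: chance that true harm is flagged.** TSDS uses the noncentral t; events use exact enumeration of two binomials with the chi-squared statistic.

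| True harm | 30/arm, 0.001 | 30/arm, 0.05 | 37/arm, 0.001 | 37/arm, 0.05 |
|---|---|---|---|---|
| TSDS 6 points worse | 8% | 50% | 12.5% | 59% |
| Events 5% vs 25% | 6% | 63% | 14% | 73% |
| Events 10% vs 30% | 5% | 50% | 10% | 59% |
| TSDS 12 points worse | 70% | 98% | 84% | 99% |
| Events 10% vs 50% | 54% | 95% | 72% | 98% |

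The 0.05 columns are two-sided, so in the harm direction they correspond to one-sided 0.025.

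**Step 4: type I error.** Looks at 0.001 (half the information) and 0.05 (final) give an overall two-sided rate of 0.0502. The boundary is sound for benefit.

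**Step 5: false harm flags under a one-sided 0.025 guideline.** With no true difference, about 2.5% per measure. For three independent measures, 1 − 0.975³ = 7.3%.

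**The case against.** A reader might infer that p = 0.001 is itself the gate to unblinding, and that material harm would therefore almost never be seen. The documents do not support that. The unblinding sentence gives no level. The Peto boundary is a separate, later statement about stopping, placed straight after the sentence on benefit, and nothing ties it to adverse events. The only general significance level in the article is 5% two-tailed. If that is the trigger, the 0.05 columns apply, and the harm direction is already tested at one-sided 0.025. Nor is harm almost never flagged across the board: at 30 per arm, a 12-point worsening or a 10% vs 50% event excess crosses even 0.001 in 70% and 54% of trials.

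It is also fair to say that the p-value is not the basis for stopping, since the nature of the events and ethics come first. The DSMB includes an independent statistician and has a standing event review that does not depend on the interim test. Events are compared between groups, so an imbalance may be visible with coded arms, and nothing forbids the DSMB from asking for the code. A symmetric boundary is a legitimate pre-specified choice, and a charter or SAP may settle the details.

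These points limit the finding but do not remove it. The conditional unblinding is a rule the article states, not a detail it omits. At 0.05 the test still misses a 6-point worsening about half the time. The six-monthly review is not stated to be by arm. No reading of the sentence keeps the investigators blinded when the DSMB is unblinded.

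**Conclusion.** The point holds as a weakness in a stated rule and should be corrected. The safety purpose is not well served when the DSMB's unblinded judgement waits on a significance test at half the planned completers. For moderate harm (6 TSDS points, or a 20-percentage-point event excess at the assumed risks), the chance of a flag is 5–8% at 30 per arm and 10–14% at 37 if the trigger is 0.001. It is 50–63% and 59–73% if the trigger is two-sided 0.05. Which row of readings applies cannot be settled from the article.

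The TSDS figures rest on the plan's SD of 11.6 and an unadjusted comparison; the event figures rest on assumed risks. The boundary creates no type I error problem, and it should not be described as the only route to stopping for harm.

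**What to change.** Amend the interim paragraph, or the DSMB charter with a reference from the protocol, to say:

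1. The DSMB receives adverse-event and TSDS data by arm, either unblinded or with the code available on its request, whether or not any test is significant.
2. The investigators stay blinded when the DSMB is unblinded.
3. The p = 0.001 boundary governs stopping for benefit on TSDS.
4. Harm is judged by the DSMB, helped by a non-binding guideline at a less extreme level agreed with it. The measures should be named, for example serious events, events of grade 3 or higher, and TSDS worsening.

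The first item matters most: if the trigger is already two-sided 0.05, a one-sided 0.025 guideline adds no sensitivity, whereas unconditional access by arm does not depend on any threshold.

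The cost is wording, with no extra participants. With no true difference, a one-sided 0.025 guideline prompts an unnecessary DSMB discussion about 2.5% of the time per measure, and up to about 7% over three independent measures. Because the guideline concerns harm only, the false-positive rate for benefit does not rise.
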